
Foster families have also been tried out in others countries (eg, United States, Belgium, Italy, Russia, and Finland), but few scientific studies have assessed its effectiveness and efficiency. A Cochrane meta-analysis published in 2015 compiled 10 studies comparing home care or foster care with nursing home care for 16,377 older participants [12]. Because of the methodological limitations of the studies included, the meta-analysis failed to determine whether or not this type of accommodation was the most efficient in terms of mortality reduction, physical function, quality of life, or hospitalization rates. Indeed, the available studies relied on small samples and had high risks of bias (design bias, evaluation bias), and the baseline characteristics of the participants were very heterogeneous. Three 30-year-old studies focusing on foster care in the United States were included [13-15]. Two of them are of interest [13,15]. Braun and Rose [13] compared 269 older participants: 100 lived in foster care, 101 in nursing homes, and 68 at home. After 3 months, Activities of Daily Living (ADL) scores only improved in the foster care group, and costs were lower than those for the other 2 groups (US $28 per day vs US $74 for nursing homes and US $45 for home). There was no difference in morbidity, defined as the number of infections, injuries, skin problems, and hospitalizations. In their randomized study on 112 participants in foster care or nursing homes, followed for 12 months, Oktay and Volland [15] found no difference in mortality rates between settings (32.0% vs 28.8%). Stabilization or improvement of ADL and cognitive status, as well as overall lower health care expenses (25% less), was in favor of foster care. Nevertheless, nursing home residents’ level of satisfaction compared favorably with that of foster family residents. In any case, available data are scarce, assessed with short follow-ups, lack essential clinical outcomes, and definitely need to be updated.

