#### Secondary Outcomes

The secondary outcomes are as follows:

Length of hospital stays during the 12-month follow-up period, in terms of days and nights, will be collected. The number of consultations with a general practitioner, a medical specialist, or paramedical professional will be reported on the case report forms (CRFs). This information will mainly be collected during interviews with the foster caregiver using the RUD-Lite scale (Resource Utilization in Dementia questionnaire) [17]. This scale assesses the use of health care resources by people with dementia. The foster caregiver will complete this questionnaire at baseline and at subsequent follow-up visits (T3, T6, T9, and T12).Global cost of hospitalization will be retrieved from the local PMSI databases.Vital status (alive or deceased) will be collected at T3, T6, T9, and T12.For the diagnosis of lower respiratory tract infections, at least two of the following symptoms must be present and a doctor must confirm the clinical evidence: (1) cough (starting or worsening), which may produce phlegm; (2) specific clinical signs during auscultation; (3) fever (≥38 °C); (4) chest pain; (5) rapid, shallow breathing (≥25 per minute); and (6) confusion or increased dependency [16].Geriatric syndromes [18] in participants will be assessed at T0, T6, and T12 as follows:Frailty will be assessed using Fried’s phenotype [19], that is, 5 predefined physical frailty criteria such as weight loss, slowness, low physical activity, weakness, and exhaustion. This will be analyzed as a dichotomous variable, that is, 1=frail and 0=not frail.The level of cognitive deterioration of the participants will be assessed using the Mini-Mental State Examination (MMSE) [20,21]. This 30-item scale assesses the severity of cognitive deterioration through items such as orientation, learning, attention, arithmetic, memory, language, and constructive praxis. The scale is rated from 0 to 30, reflecting the level of cognitive impairment.Depression will be assessed using the Center for Epidemiologic Studies—Depression Scale (CES-D) [22] validated in French by Fuhrer and Rouillon [23]. This 20-item questionnaire assesses depressive symptomatology, including 4 positive polarity items (happiness, self-worth, confidence, and enjoyment). The frequency of symptom occurrence during the past week is assessed by the participant using a 4-point Likert scale (never, occasionally, quite often, and frequently). The score ranges from 0 to 60. The higher the score, the more significant the symptomatology. High depressive symptomatology corresponds to a score above 16. Data will be collected at baseline, T6, and T12. For statistical analyses, the variable will be dichotomized (1=presence of depression and 0=absence of depression).The total number of medications taken by participants will be collected directly from the RUD-Lite questionnaire, at T0, T3, T6, T9, and T12, to assess polypharmacy.The total number of falls since the last visit will be collected at each follow-up from the foster caregivers.The Short Physical Performance Battery [24,25] will help to assess sarcopenia. Three subtests measure lower-extremity functions: keeping balance (feet side-by-side, semitandem, tandem balance position, to be kept for 10 s each); walking 4 m at usual pace, yielding a gait speed ratio (meter per second); standing up and sitting down 5 times as quickly as possible with the arms folded. Each movement is scored 0-4 points out of a total score from 0 to 12, with higher scores showing better physical performance. If the total score is below 8, there is a risk of sarcopenia. For the analyses, the variable will be dichotomized accordingly (1=sarcopenia; 0=no sarcopenia).Undernutrition will be assessed with the short version of the Mini Nutritional Assessment [26]. This questionnaire assesses nutritional status. A score below 12 indicates probable undernutrition. For the analyses, the variable will be dichotomized accordingly (1=undernutrition; 0=no undernutrition).Sensory impairments (audition and vision) will be collected by directly asking the foster caregiver. Variables will be dichotomized accordingly (1=hearing/vision impairment; 0=hearing/vision impairment).The level of independence in ADL and incontinence will be assessed using the Katz scale [27], a 6-item scale assessing independence in 6 basic ADLs: bathing, toileting, transferring, eating, dressing, and incontinence. For each activity, a score of 1 indicates complete autonomy, a score of 0.5 indicates partial autonomy, and a score of 0 indicates complete dependency.The level of independence in IADL will be assessed using the Lawton IADL scale [28]. The Lawton IADL scale measures 8 items: using the telephone, shopping, preparing food, housekeeping, doing laundry, using transportation, handling medications, and handling finances. The score is from 0 to 8; a score of 8 indicates total autonomy, and 0 indicates total dependency. In France, the Autonomy, Gerontology Iso-Resources (AGGIR) questionnaire has been developed by public authorities to quickly assess the degree of dependency of elderly people and assign a dependency group, ranging from 0 (bedridden, completely dependent) to 6 (no help required, the person is autonomous in everyday activities).Psychological and behavioral symptoms in dementia will be assessed with the short version of the NeuroPsychiatric Inventory or NPI [29,30]. This scale assesses the psychological, behavioral manifestations (agitation, hallucinations, apathy, etc), neurovegetative symptoms (sleep and appetite), and the impact on the professional’s workload.Feeling of loneliness will be captured with the 14th item of the CES-D [22,23]: I felt lonely. The answer possibilities are never, occasionally, often, and frequently. The answer “often” or “frequently” indicates a feeling of loneliness.Risk of developing pressure ulcers will be assessed with the Braden scale, and pressure ulcers will be classified according to the National Pressure Ulcer Advisory Panel, European Pressure Ulcer Advisory Panel, and Pan Pacific Pressure Injury Alliance [31].Quality of life and adaptation will be assessed as follows:Quality of life of the participant will be assessed at baseline, T6, and T12 using the Questionnaire Quality of Life—Alzheimer’s Disease (QoL-AD) [32,33]. This 13-item questionnaire assesses the participant’s physical condition, mood, relationships with friends and family, financial difficulties, and overall quality of life. The questionnaire is to be administered to both seniors and caregivers, and thus is based on both self-rated health problems and proxy ratings from foster families. The items are evaluated using a 4-point ordinal scale ranging from poor to excellent, with a total score ranging from 13 to 52. For the weighted score, the participant’s score is multiplied by 2, the caregiver’s score is added, and the total is divided by 3 to bring the score back to the initial scale. In the proxy version, the foster caregiver will be asked to try to give the answer they think the participant would give.Health-related quality of life of the participant will be assessed with the EQ-5D questionnaire [34]. This questionnaire assesses health conditions. It is the most widely used questionnaire in medicoeconomic analyses. It allows health outcomes to be assessed in terms of quality-adjusted life-years (QALYs). This indicator summarizes the length and quality of life in a single figure. The result of a cost-utility analysis is expressed in terms of the cost of gaining one QALY (ie, 1 year lived in perfect health). To estimate QALY, health-related quality of life is designed on a continuum from 0 (death) to 1 (perfect health). Each health status is thus assigned a weight of 0 to 1; the higher the score, the higher the corresponding quality of life.On the first page, the participant has to indicate, for each of the 5 dimensions assessed (mobility, independence, routine activities, pain or discomfort, and anxiety or depression), the state in which he or she finds himself or herself, by choosing 1 of the 3 options with increasing severity: no problems, problems, and extreme problems. The answers can be combined to describe the residents’ health status, using a 5-digit number corresponding to the 5 answers.On the second page, the participant assesses his or her overall health using a standard vertical 20 cm visual analog scale (EuroQol visual analog scale), graduated from 0 to 100, from “best imaginable state of health” to “worst imaginable state of health.”The score will be collected at T0, T6, and T12. The interviewer will use both the participant version and the proxy version. In the proxy version, the foster caregiver will be asked to try to give the answer they think the participant would give.Adaptation to the nursing home setting will be assessed at baseline, T6, and T12 using the Castonguay and Ferron scale [35]. This is a 17-item scale designed to identify who do not experience a favorable adaptation to the living conditions in nursing homes. The participants answer yes or no to a series of statements about their daily life and habits in the residence. A score of 16 or 17 indicates a good general adaptation to life in the residence, whereas a score of 11 or less indicates significant difficulties.Foster caregivers’ quality of life will be assessed with the Medical Outcomes Study Short-Form General Health Survey—36 items (SF-36) [36], a widely validated health-related quality of life questionnaire that uses questions on physical, social, and psychological domains.Symptoms of burnout will be assessed with the Professional Quality of Life (Pro-QoL) scale [37]. This 30-item questionnaire yields 3 domain-specific scores: compassion fatigue (ie, the pleasure of being able to do your job well), work satisfaction, and burnout in helping professionals.

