### Data Analysis

First, the analysis will describe the number of included participants, the inclusion curve (evolution of the number of people included between the first and last inclusion), the number of theoretical visits, the number of visits actually made, and the ratio of both (number of visits made or number of theoretical visits).

A description of the rate and causes of death and study dropout will also be provided.

The following quantitative variables described in terms of number of staff, mean, and interindividual SD and 95% CI of the mean, median, range, and IQR values: number of hospitalizations, total length of hospitalization, total cost related to hospitalizations, total number of consultations with a general practitioner, total cost of low respiratory infections, total number of falls, MMSE score, total number of drugs, NPI score, QoL-AD score, SF-36 score, and Pro-QoL score.

Qualitative variables (ordinal: AGGIR grid, feeling of loneliness; dichotomous: vital status; presence or absence: frailty syndrome, depression, undernutrition, visual impairment, hearing impairment, incontinence, ADL dependency, IADL dependence) of participants at inclusion will be described in terms of frequency and number.

Comparisons between the 3 times (T0, T6, and T12) will be performed using repeated-measures ANOVA for quantitative variables and the Cochran-Armitage test for trend for qualitative variables.

Statistical analyses will be performed using the RStudio software (version 2.7; Posit Software).

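### Katz ADL and Lawton IADL are defined as graded scores but analysed only as dependency present or absent, at an unstated cut-off, which discards most of the information on functional change

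*Protocol article*

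**What the plan says.** Under Secondary Outcomes, the Katz scale has six items, and for each "a score of 1 indicates complete autonomy, a score of 0.5 indicates partial autonomy, and a score of 0 indicates complete dependency". Of the Lawton scale the same section says: "The score is from 0 to 8; a score of 8 indicates total autonomy, and 0 indicates total dependency". For CES-D, SPPB and MNA-SF that section gives a threshold and announces a dichotomy. For Katz and Lawton it does neither.

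The Data Analysis section sorts the variables into two lists. The quantitative list ends with "total number of falls, MMSE score, total number of drugs, NPI score, QoL-AD score, SF-36 score, and Pro-QoL score"; no ADL or IADL score appears anywhere in it. The qualitative list begins "Qualitative variables (ordinal: AGGIR grid, feeling of loneliness; dichotomous: vital status" and, among the presence-or-absence variables, ends with "hearing impairment, incontinence, ADL dependency, IADL dependence) of participants at inclusion will be described in terms of frequency and number". Comparisons across T0, T6 and T12 then use repeated-measures ANOVA for quantitative variables and the Cochran-Armitage trend test for qualitative ones.

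Table 2 schedules the ADL, IADL and AGGIR scales at all three on-site visits.

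**The concern.** The two sections do not fit together. The outcome definitions measure how independent a resident is; the analysis asks only whether dependency is present. Anyone following the Data Analysis section would test change in function on a yes/no variable whose threshold is nowhere given. If the words about inclusion restrict the dichotomy to baseline, no follow-up analysis of either scale is named at all.

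This matters for the study's own questions. The Introduction wants foster care assessed according to how severe ADL dependence is. The abstract's Conclusions and the Discussion promise to follow geriatric syndromes over time, and Objectives counts dependency among those syndromes. The earlier foster-care evidence that the Introduction wants updated includes a score result: "After 3 months, Activities of Daily Living (ADL) scores only improved in the foster care group". A proportion of dependent residents cannot be set beside that.

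A threshold that is not fixed in advance can also be chosen after the data are seen.

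**Working it through.** **The plan's own figures.** The protocol gives no power or precision figure for function. Its only calculated figures are the confidence-interval half-widths for hospitalization with 250 participants. They reproduce as 1.96 × √(0.15 × 0.85/250) = 4.4% and 1.96 × √(0.30 × 0.70/250) = 5.7%, and have no bearing here.

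**Inputs from the document.** Katz: 6 items, steps of 0.5, total 0-6. Lawton: 0-8. Planned N 250 (Study Sample); recruited N 109 (Results). Eligibility sets no dependency threshold, and no ADL or IADL distribution is given.

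**Assumptions.** Mean loss of 0.5 points from T0 to T12. Katz mean 3.5 (SD 2.0) or 4.5 (SD 1.5), SD of change 1.3. Lawton mean 2 or 4, SD 2, SD of change 1.5. Complete pairs 80 or 109; 80 corresponds to losing 29/109 = 27%. Latent normal scores are rounded to the scale step and clipped to the scale range.

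**Step 1. Share counted as dependent if any loss counts.** With rounding, Katz below 6 means a latent score below 5.75, and Lawton below 8 means a latent score below 7.5. The T12 column keeps the T0 spread.

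| Scale | T0 | T12 after a loss of 0.5 |
|---|---|---|
| Katz, mean 3.5, SD 2.0 | Φ(2.25/2.0) = 87% | Φ(2.75/2.0) = 92% |
| Katz, mean 4.5, SD 1.5 | Φ(1.25/1.5) = 80% | Φ(1.75/1.5) = 88% |
| Lawton, mean 2, SD 2 | Φ(5.5/2) = 99.7% | Φ(6.0/2) = 99.9% |
| Lawton, mean 4, SD 2 | Φ(3.5/2) = 96% | Φ(4.0/2) = 98% |

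The Katz dichotomy still has some room to move. The Lawton dichotomy has almost none.

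**Step 2. Power for the Katz total.** Before rounding and clipping, the standardized effect is 0.5/(1.3/√80) = 3.44, so power ≈ Φ(3.44 − 1.96) = 0.93. With 109 pairs it is 0.5/(1.3/√109) = 4.02, giving Φ(2.06) = 0.98. Simulation with rounding and clipping gives 0.88 to 0.98 at 80 pairs, depending on how the change is modelled.

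**Step 3. Power for Katz below 6 (exact McNemar, two-sided 5%).** The answer depends on the model for T12:
- Change noise added to the T0 score, so that the spread grows by T12: 0.02 to 0.03 at 80 pairs. The wider spread offsets the mean loss at the top of the scale.
- Equal spread at both times: 0.13 to 0.31 at 80 pairs and 0.21 to 0.43 at 109.

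With the cut at below 5 and equal spread, power at 80 pairs is 0.27 to 0.48.

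**Step 4. A second, item-level model.** Six items scored 0/0.5/1, baseline means 1.7 to 3.5, decline about 0.4 to 0.5 points, N = 109. Power of the graded score is 0.95 to 0.98. For the dichotomy:

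| Dependent if Katz is | Prevalence at T0 | McNemar | Cochran-Armitage (T0 v T12) |
|---|---|---|---|
| below 6 | 92-99% | 0.00-0.13 | 0.00-0.12 |
| below 5 | 74-96% | 0.04-0.45 | 0.07-0.27 |
| below 3.5 | 43-84% | 0.34-0.68 | 0.20-0.35 |

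Cochran-Armitage is the test the plan names. At N = 250 the graded score has power of about 1.00, and McNemar reaches 0.00-0.36, 0.22-0.87 and 0.78-0.97 for the three cut-offs.

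**Step 5. Lawton.** At 80 pairs, power for the total is 0.40 to 0.78, lower than for Katz because some residents already sit at zero. For below 8 it is 0 to 0.01 by McNemar, and about 0.03 at most with 109 pairs.

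**The case against.** The strongest reply is that a graded dependency measure is already in the longitudinal analysis. AGGIR is described as "ranging from 0 (bedridden, completely dependent) to 6 (no help required, the person is autonomous in everyday activities", is listed as ordinal, is collected at T0, T6 and T12, and falls under the comparison over time. This stands. A reader might infer from the ADL and IADL coding that the study cannot show functional change, or would report none while residents decline. The document does not support that, both because of AGGIR and because a dichotomized Katz retains some power. AGGIR is nevertheless a separate instrument that assigns a dependency group. It is neither the Katz score nor the Lawton score.

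Second, the ceiling is an inference. The residents are repeatedly called dependent, but entry requires no level of dependency, no distribution is reported, and no passage equates dependency with anything short of full autonomy. With a lower cut-off the ceiling largely goes. This also stands, and it is why the size must be given as a range.

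Third, the prevalence objective needs presence or absence, so the dichotomies have a proper use. Agreed; the point is that they should not be the only form.

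Fourth, a condensed article may leave a cut-off to the full protocol or analysis plan. True of the cut-off alone. But the article itself fixes the form of the variables and the test over time, and that choice conflicts with its own graded definitions.

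**Conclusion.** The point holds as a weakness in a stated analysis of secondary outcomes. Two graded scales are reduced to yes/no variables for the comparison over time, and neither total is analysed. That much is on the page and needs no assumption.

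The size does rest on assumptions: the distributions, a half-point loss, 80 to 109 pairs, and the cut-off. Within them, power for Katz is about 0.9 or higher with the total, against roughly 0.02 to 0.45 for any-loss dependency at baseline means of 3.5 to 4.5. A lower cut-off usually closes only part of the gap; it closes most of it in some settings, such as below 3.5 with 250 residents. Lawton below 8 is almost blind to change, at about 0 to 0.03. The direction is the same in every scenario examined; the amount is not established by the document.

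**What to change.** In Data Analysis, add the Katz total (0-6) and the Lawton total (0-8) to the quantitative variables, and base the T0/T6/T12 comparison of function on them. Keep ADL and IADL dependency as dichotomies for the prevalence objective, and state the cut-off for each in advance, as is done for CES-D, SPPB and MNA-SF. AGGIR can stay as it is.

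The cost is a change of wording and two more rows in the results. No new data are needed, since both scales are already scheduled at all three visits.

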**Conclusions:**

Foster families are a potentially innovative way to accommodate dependent older people. This study could help define the clinical profile of older people adapted to foster families in the transition from frailty to dependency. The effectiveness of foster families, in terms of hospitalizations and mortality, will be compared with other models of care, particularly nursing homes. In this setting, a twin study carried out in nursing homes in Guadeloupe with similar aims and outcomes will be conducted. Beyond mortality and morbidity, the numerous outcomes will allow us to assess the evolution of geriatric syndromes over time.

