## Methods

### Overview

The KASAF is a prospective, longitudinal cohort carried out in Guadeloupe (French West Indies), France, among foster families for older adults. This study will collect the socio-medico-economic data of older residents of foster families over a year, with a focus on hospital admissions. We will collect data using face-to-face interviews with the participants and their foster caregivers at baseline and after 6 and 12 months, and using phone interviews with the foster caregivers after 3 and 9 months.

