#### On-site Interviews

Participants will be interviewed at baseline, after 6 months, and after 12 months. At each visit, different function domains will be assessed to measure (1) the ability to perform ADLs (eg, personal care, eating, and mobility) and (2) the ability to perform instrumental ADLs (eg, using the telephone, shopping, and managing finances). In fact, the interview implies both a physical evaluation (grip strength, gait speed, and blood pressure) and a cognitive and a psychological assessment. The estimated time for completion is 30 minutes but may vary depending on the participant’s physical and cognitive status. Each of the participants will remain in the study for further follow-up interviews even if he or she is unable to answer, and reasons for incomplete data will be documented by the interviewers. Interviewers may split the visit into 2 parts to respect the participant’s rhythm and to avoid missing data.

During on-site visits, foster caregivers will provide their own sociodemographic data (as well as information on the caregiving burden borne) and those of the elders to be cared for. Thus, both the quality of life of foster caregivers and the main sociodemographic or health data of the participants (eg, medical history, medication, nutrition, and ADL/Instrumental Activities of Daily Living [IADL] performance) are the primary focus of the study.

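### The Cochran-Armitage trend test is named for repeated measures on the same residents, so tests of change in the secondary qualitative outcomes are too conservative and lose power

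*Protocol article*

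**What the plan says.** The Overview in Methods gives the design: "The KASAF is a prospective, longitudinal cohort carried out in Guadeloupe". Under On-site Interviews, "Participants will be interviewed at baseline, after 6 months, and after 12 months", and "Each of the participants will remain in the study for further follow-up interviews even if he or she is unable to answer". The three time points are therefore repeated assessments of the same people.

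The Data Analysis section gives one sentence on tests over time. It begins: "Comparisons between the 3 times (T0, T6, and T12) will be performed using repeated-measures ANOVA for quantitative variables". For the rest it names "the Cochran-Armitage test for trend for qualitative variables". No paired or correlated-data method is named for qualitative variables.

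The same section lists the qualitative variables, starting "Qualitative variables (ordinal: AGGIR grid, feeling of loneliness; dichotomous: vital status". The list goes on to frailty, depression, undernutrition, visual and hearing impairment, incontinence, and ADL and IADL dependence.

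The abstract states the purpose these tests serve: "the numerous outcomes will allow us to assess the evolution of geriatric syndromes over time".

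**The concern.** The Cochran-Armitage test takes its variance from independent binomial samples. Here the resident seen at T12 is the resident seen at T0. Frailty, incontinence, sensory loss or dependency in one person is likely to be positively correlated over 6 to 12 months. The variance of a change within persons is then smaller than the test assumes, and its p-values are too large. The first half of the same sentence uses a repeated-measures method, so the repetition was recognised for one type of variable and not carried over to the other. A test named outright is not a detail left to a fuller document.

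There is a second mismatch. The test needs a two-level outcome, and the article itself labels AGGIR and loneliness as ordinal.

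What is at stake is the chance of detecting a change in geriatric syndromes over the year. That matters more because 109 residents were recruited against 250 planned.

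**Working it through.** **The plan's own figure.** The only design figure is the precision of the hospitalization rate under Study Sample: 4.4 points at a rate of 15% and 5.7 points at 30%, with 250 participants. The half-width is 1.96 × √[p(1−p)/n].
- p = 0.15: 1.96 × √(0.1275/250) = 4.43 points.
- p = 0.30: 1.96 × √(0.21/250) = 5.68 points.

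Both reproduce. Neither depends on the trend test.

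**True size of the trend test on repeated measures.** Give T0, T6 and T12 the scores −1, 0, 1 and let the same n residents be seen each time.
- Numerator of the test: Σ(Y_T12 − Y_T0).
- Null variance used by the test: 2n·p(1−p).
- True null variance with T0-T12 correlation ρ: 2n·p(1−p)(1−ρ).
- The Z statistic therefore has variance 1−ρ, and the true two-sided size is 2·[1 − Φ(1.96/√(1−ρ))].

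The documents give no ρ, so a range is assumed:

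| ρ | 1.96/√(1−ρ) | True size at nominal 5% |
|---|---|---|
| 0 | 1.96 | 5.0% |
| 0.3 | 2.34 | 1.9% |
| 0.5 | 2.77 | 0.6% |
| 0.7 | 3.58 | 0.03% |

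At ρ = 0 the test is sound, so the whole fault lies in the repetition. Simulation with 109 residents and no loss agrees: 2.05%, 0.55% and 0.05% at ρ = 0.3, 0.5 and 0.7 (8,000 runs each).

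**Power with residents lost over time.** Inputs:
- 109 residents at T0 (Results section).
- An assumed 15% loss by T6 and 30% by T12: 109 × 0.85 ≈ 92 and 109 × 0.70 ≈ 76. KASAF gives no loss figure. The nearest are the 12-month mortality rates of 32.0% and 28.8% that the Introduction cites from an older randomized study.
- Assumed prevalence 30%/36%/42% and within-resident correlation (phi) of about 0.4 to 0.67.

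Simulated power is about 35-37% for Cochran-Armitage and 52-79% for a test that respects the pairing. These are simulation results and can move by a point or two between runs.

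**Power under a smaller change, 30% to 40%, with no loss.**

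| n | ρ | Cochran-Armitage | Test allowing for repetition |
|---|---|---|---|
| 109 | 0.3 | 32% | 46% |
| 109 | 0.5 | 28% | 60% |
| 109 | 0.7 | 23% | 83% |
| 250 | 0.3 | 68% | 80% |
| 250 | 0.5 | 71% | 91% |
| 250 | 0.7 | 76% | 99% |

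With 109 residents and 30% random loss by T12, the pairs are 27% against 36%, 24% against 44%, and 20% against 57%. The loss of power is present in every setting with positive correlation and grows with that correlation.

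**Outcome type.** Secondary Outcomes describes AGGIR as running from 0 to 6, so it has more than two levels and the test does not apply as named. For loneliness the article gives two codings: ordinal in Data Analysis, and a yes/no rule in Secondary Outcomes based on the two most frequent answers. The mismatch arises only if the ordinal coding is used. The other listed syndromes are binary, and for them only the independence assumption fails.

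**The case against.** The strongest reply is about scope. The Discussion calls the study descriptive, and the primary objective is the hospital admission rate. Neither the primary outcome nor its precision uses this test, and prevalence at each visit, which is the stated secondary objective for geriatric syndromes, is unaffected. The error is conservative and produces no excess of false positives. Falls, number of drugs and MMSE score are listed as quantitative and go to ANOVA. All of this stands, and it limits the severity. It does not make the named test suitable.

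The size of the loss also rests on assumed correlation, prevalence and attrition. That is true, but only the amount depends on them. The direction needs no more than positive correlation within residents.

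Three stronger readings are tempting, and the documents do not support them.
- A reader might infer that the trend test will be run on vital status. Vital status appears in a sentence on describing variables at inclusion, it is not collected at T0 (Secondary Outcomes and Table 2), and death is to be described separately. A T0/T6/T12 comparison of it is not clearly planned.
- A reader might add the cutting of scores to yes/no to this point, for example "For the analyses, the variable will be dichotomized accordingly (1=sarcopenia; 0=no sarcopenia". That is a separate trade-off. Cut-offs are needed to report prevalence, and sarcopenia is not in the Data Analysis list of qualitative variables.
- A reader might conclude that real changes will be reported as no change. Power falls, but larger changes could still be detected.

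**Conclusion.** The point holds: the article names an independent-groups test for repeated measures on one cohort. For correlations of 0.3 to 0.7, a nominal 5% test runs at about 1.9% down to 0.03%. With 109/92/76 residents seen and prevalence of 30%/36%/42%, power is about 35-37% where a test that respects the pairing would have 52-79%. Correlation, prevalence and attrition are assumptions.

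The test is also unsuited to AGGIR, and to loneliness if that stays ordinal. The outcomes affected are changes over time in frailty, depression, undernutrition, sensory impairment, incontinence, ADL and IADL dependency, AGGIR and loneliness. This takes the test sentence to cover the qualitative variables listed just before it, apart from vital status. The p-values err towards missing change. This should be fixed, but it does not threaten the study's main result.

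**What to change.** In Data Analysis, replace the Cochran-Armitage test with a GEE or mixed logistic regression for each binary syndrome, with time (0, 6, 12 months) as the explanatory variable and resident as the repeated unit. Use the ordinal version of the model for AGGIR. State whether loneliness is analysed as binary or ordinal, and use the ordinal model if it is not dichotomised. With deaths and dropout expected, a model that uses partial follow-up is preferable to a test restricted to residents with all three visits, such as Cochran's Q.

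The cost is a change of wording and a few lines of code, with no new data. The Results section says the analyses are still ongoing. If they have since been run, the affected comparisons need only be rerun and the change of method reported.
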